#### Recruitment

We will recruit participants by posting advertisements on WeChat. Additionally, a series of educational lectures on shallow needling for chronic insomnia will be held at the Affiliated People’s Hospital of the Fujian University of Traditional Chinese Medicine to attract potential participants. All participants who meet the selection criteria will sign an informed consent form after understanding the purpose of the study and the program implementation process. Individuals’ personal information will be collected and securely stored in a separate cabinet to ensure confidentiality. The inclusion and exclusion criteria are detailed in Textbox 1.

Textbox 1.Inclusion and exclusion criteria.
**Inclusion criteria**
Patients who meet the diagnostic criteriaPatients with insomnia aged 18 to 65 yearsPittsburgh Sleep Quality Index score range from 7 to 15The duration of the disease ≥3 monthsNo communication and cognitive impairmentVoluntary enrollment and can sign informed consent form
**Exclusion criteria**
Secondary insomniaUnwillingness to receive shallow needling therapyPregnant or lactating women, or those who intend to become pregnantPatients with heart, liver, kidney, lung, brain, and other serious organic diseasesParticipants in other studies that may influence the results of this study

#### Randomization and Blinding

##### Randomization

The randomization sequence will be computer-generated by an independent statistician using SPSS Statistics (version 23.0; IBM Corp), using a block randomization method with a 1:1 allocation ratio. Sequentially numbered, opaque, sealed envelopes will be used to implement allocation concealment. Each envelope will contain a card specifying the random number, sequence number, and group assignment. After obtaining written informed consent, eligible participants will be assigned to either the treatment group or the control group by opening the next consecutively numbered envelope, and it is ensured that the random allocation sequence remains unknown to the researchers before enrollment to prevent selection bias.

##### 
Blinding

Due to the specific nature of the shallow needling procedure, we could not blind the investigators and participants, but outcome assessors and statisticians would be unaware of the trial-group assignments.

### Interventions

#### The Control Group

Participants in the control group will receive oral eszopiclone (trade name: Itannin, manufactured by Chengdu Kanghong Pharmaceutical Group Co, Ltd, approval number: Sinopharm H20100074) at a dose of 1 mg before bedtime daily, for 4 weeks.

#### The Treatment Group

In addition to eszopiclone (same as the control group), participants will receive shallow needling therapy daily, 5 times a week, for 4 weeks.

The selected acupoints are Shangen (located at the intersection of the line connecting the inner canthi of both eyes and the midline of the nose), Zhenjing (located 0.3 cun above Yintang [GV29], with 1 cun being approximately the width of the patient’s thumb at the knuckle), and Ezhong (located at the midpoint of the line connecting the hairline and Yintang). The locations of the acupoints are shown in Figure 4.

**Figure 4. F4:**
[figure not shown]
Anatomical locations of the acupoints.

Before treatment, the participants are told to lie in a supine position in a quiet environment. The practitioner wraps a small piece of disinfected cotton around the tip of the needle and places it on the acupoint, applying light pressure without penetrating the skin of the patient. The practitioner uses the pad of the thumb to stabilize the needle handle, ensuring that the tip is perpendicular to the surface of the acupoint. The practitioner uses the edge of the middle fingernail to continuously scrape upward and downward along the needle handle, creating gentle and uniform vibrations. Each cycle of 81 scraping motions is 1 dose of stimulation, with 3 doses per acupoint.

The shallow needling will be performed by 3 licensed acupuncturists with at least 5 years of clinical experience in acupuncture. They will receive comprehensive training on the study procedures and shallow needling techniques before participating in this study.

In order to ensure the accuracy and reliability of the results of this trial, the use of other disease-related treatments was prohibited during the trial.

#### Follow-Up

The aim of the follow-up procedure is to assess the long-term effects of shallow needling for chronic PI. Follow-up assessments will be conducted after the 4-week intervention program. No further interventions will be provided during this period. Participants will obtain the same outcome measures as before the intervention. Regular reminders will be provided to ensure adherence, and any adverse events will be recorded and monitored by the researchers. This follow-up procedure is essential for understanding the long-term effects of shallow needling.

### Outcome Measures

#### Primary Outcome Measures

PSQI [29] is a questionnaire used to assess an individual’s sleep quality, with good reliability and validity, indicated by a Cronbach α coefficient of 0.83 and a test-retest reliability of 0.85 [30]. It consists of 7 components: subjective sleep quality, sleep latency, sleep duration, habitual sleep efficiency, sleep disturbances, use of sleeping medication, and daytime dysfunction. The total score ranges from 0 to 21. A global PSQI score greater than 7 indicates the presence of sleep disorders, with higher scores reflecting poorer sleep quality. PSQI will be assessed before treatment, after treatment, and 4 weeks after treatment completion (follow-up).

#### Secondary Outcome Measures

##### Overview

Hamilton anxiety scale [31] consists of 14 items with a scale ranging from 0 to 4. Higher scores indicate more severe anxiety levels. This scale is usually used to measure the levels of anxiety. The evaluation time points are the same as those for the primary outcome indicator.

Insomnia Severity Index [32] is a self-assessment scale used to measure an individual’s experience of insomnia. It consists of 7 items, each rated on a scale from 0 to 4. Higher scores indicate greater severity of insomnia. The total score ranges from 0 to 28, categorized as follows: 0‐7 (no insomnia), 8‐14 (mild insomnia), 15‐21 (moderate insomnia), and 22‐28 (severe insomnia). Assessment time points align with the primary outcome measure.

##### Objective Sleep Structure

Overnight sleep monitoring will be conducted using a polysomnography device (model: Alice 6 LDxN/LDxS, purchased from Respironics). The parameters, including total sleep time, sleep latency, wake after sleep onset, sleep efficiency, and the percentage of total sleep time spent in rapid eye movement (REM) and non-REM sleep stages 1, 2, and 3/4 (with stages 3 and 4 combined as deep sleep, reported as REM%, N1%, N2%, and N3%) were selected for outcome measurement. Participants will undergo sleep monitoring from 7 PM to 7 AM on the day before treatment and the day after the completion of the treatment course in the hospital.

##### Serum Neurotransmitter Detection

Fasting blood samples (5 mL) will be collected from participants between 8 AM and 10 AM. Blood samples will be centrifuged at 3000 rpm to separate the serum and subsequently stored in a laboratory freezer at −80°C. The concentrations of dopamine, norepinephrine, and melatonin will be measured using enzyme-linked immunosorbent assay kits, according to the manufacturer’s instructions (Shanghai Enzyme-linked Biotechnology Co, Ltd). Measurements will be taken 1 day before treatment, 1 day after the completion of the treatment course, and at a 4-week follow-up.

##### Thalamic MRS

Scans will be performed with a 3.0T magnetic resonance scanner (Philips Ingenia CX 3.0T, Philips Healthcare). Participants will be required to keep their eyes closed, remain at rest, and stay awake during scanning. The bilateral thalamus will be selected as the region of interest, and all scans will be performed by the same experienced radiologist.

##### Imaging Parameters

The s2D_PRESS_144 sequence will be used for data acquisition, with a total scan duration of 5 minutes and 52 seconds. The field of view of the equipment will be anteroposterior, with a diameter of 230 mm. Right-left diameter will be 192 mm. The size of the acquisition voxel will be 10.0×10.1×15.0 mm. The echo time will be 144 milliseconds. The repetition time will be 2000 milliseconds. The acquisition matrix will be 23×19. The slice thickness will be 15 mm and the scan percentage will be 100%.

After the acquisition of MRS data, postprocessing will be executed using the Magnetic Resonance Spectro View software installed on the Intellispace Portal workstation. This postprocessing will mainly involve tasks such as noise reduction, frequency calibration, and baseline correction. Subsequently, the processed data will be analyzed to measure the levels of GABA, Glx, N-acetylaspartate, and choline-containing compounds in the thalamic region. The software will identify the characteristic peaks of these metabolites in the MRS spectra and calculate their relative concentrations based on the peak areas and predefined algorithms. MRS will be conducted before and 4 weeks after treatment to assess the changes in central neurotransmitter and thalamic metabolite levels.

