### Hypotheses

We hypothesize the following:

Compared with the control group, the symptoms of insomnia and anxiety in the treatment group were significantly relieved after treatment according to the scale evaluation. At the same time, according to the objective sleep outcome test results, the sleep treatment of the treatment group was further proved to be improved.Compared with the control group, the levels of serum neurotransmitters, central neurotransmitters, and metabolites in the treatment group were significantly improved, reflecting the better regulatory effect of shallow needling.

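### The stated MRS acquisition (3.0T PRESS, echo time 144 ms, 1.5 mL voxel, peak areas) is not expected to give a valid thalamic GABA value and supports Glx only weakly

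*Protocol article*

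**What the plan says.** The Thalamic MRS section of the protocol article specifies a 3.0T scanner with the bilateral thalamus as region of interest. Imaging Parameters then fixes a single acquisition: "The s2D_PRESS_144 sequence will be used for data acquisition, with a total scan duration of 5 minutes and 52 seconds". It adds: "The echo time will be 144 milliseconds"; "The repetition time will be 2000 milliseconds"; "The size of the acquisition voxel will be 10.0×10.1×15.0 mm"; "The acquisition matrix will be 23×19".

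From these data the software is to "measure the levels of GABA, Glx, N-acetylaspartate, and choline-containing compounds in the thalamic region". The method is to identify each metabolite's characteristic peak and "calculate their relative concentrations based on the peak areas and predefined algorithms". Preprocessing covers noise reduction, frequency calibration and baseline correction. The section mentions no spectral editing, no second acquisition at short echo time, no basis-set fit and no spectral quality limit.

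The Introduction builds the thalamic rationale on GABA and Glx. The second hypothesis, under Hypotheses, is wider: "the levels of serum neurotransmitters, central neurotransmitters, and metabolites in the treatment group were significantly improved". The Abstract lists MRS among the secondary outcomes.

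**The concern.** A peak-area method needs a peak that can be told apart from its neighbours. At 3T the GABA resonance near 3.0 ppm lies under the much larger creatine peak, and GABA's other resonances lie close to Glx and NAA. A long echo time in a small voxel also leaves little signal. The acquisition as described suits strong, isolated peaks such as NAA and choline better than GABA.

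This is a conflict between a stated method and a stated outcome. The article gives the sequence, echo time, repetition time, voxel, matrix, scan time, software and quantification principle, so the point does not turn on detail left out for brevity.

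At stake is the part of the second hypothesis that concerns central neurotransmitters. Of the four MRS measures only GABA and Glx are neurotransmitter measures, while the serum assays are peripheral. If the software returns a number labelled GABA, the trial could report an effect, or no effect, on thalamic GABA when the number mostly reflects something else.

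**Working it through.** **Inputs from the article:** field 3.0T; echo time (TE) 144 ms; repetition time 2000 ms; field of view 230 × 192 mm; matrix 23 × 19; slice 15 mm; scan time 5 min 52 s.

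**Assumptions, not in the article:** proton frequency 127.7 MHz; GABA near 3.01 ppm and creatine near 3.03 ppm; in vivo line width 5–8 Hz; GABA 1–2 mM (2 protons) and creatine 6–10 mM (3 protons); GABA T2 60–120 ms and creatine T2 150 ms; T2 of 60–180 ms for the general signal-loss check; GABA coupling constant J about 7.3 Hz.

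**1. The plan's own voxel figure.** 230/23 = 10.0 mm and 192/19 = 10.1 mm, which agree with the stated voxel. Volume = 10.0 × 10.1 × 15.0 = 1515 mm³ = 1.515 mL.

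**2. Scan time.** 352 s / 2 s = 176 repetitions. A full 23 × 19 grid has 437 steps, or 874 s at one step per repetition. On that basis the scan is accelerated or partly sampled, with no room for repeated averages. This is not an error, but it adds nothing to offset the low signal of a small voxel.

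**3. Overlap.** (3.03 − 3.01) × 127.7 = 2.6 Hz, below a line width of 5–8 Hz. There is no separate GABA peak at 3.0 ppm to integrate.

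**4. Signal left after T2 decay, exp(−TE/T2).**

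| T2 | TE 144 ms | TE 30 ms |
|---|---|---|
| 60 ms | 0.09 | 0.61 |
| 120 ms | 0.30 | 0.78 |
| 180 ms | 0.45 | 0.85 |

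So 9–45% remains at 144 ms, against 61–85% at 30 ms.

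**5. GABA area relative to creatine area at TE 144 ms.** r = (GABA × 2 × exp(−144/T2 GABA)) / (creatine × 3 × exp(−144/150)), where exp(−144/150) = 0.383.
- Low end (GABA 1 mM, creatine 10 mM, GABA T2 60 ms): (2 × 0.0907)/(30 × 0.383) = 0.016.
- High end (GABA 2 mM, creatine 6 mM, GABA T2 120 ms): (4 × 0.301)/(18 × 0.383) = 0.175.

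GABA is thus about 2–17% of the creatine signal. As a share of the combined peak, r/(1 + r), this is 1.6% to 14.9%.

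**6. What a change in GABA would do.** As an illustration, a 20% change in GABA alone moves the combined peak by 0.20 × 1.6% = 0.3% up to 0.20 × 14.9% = 3.0%.

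**7. Phase modulation from J-coupling.** cos(2π × 7.3 × 0.144) = 0.95. The GABA triplet at 3.0 ppm is almost refocused at this echo time, so dephasing is not the obstacle. Overlap, T2 loss and low signal are.

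**The case against.** **The documents say nothing about detectability.** That the sequence is unedited is inferred from its name and from the absence of any editing step, and a fuller imaging protocol may exist. This stands as a limit on wording: the conclusion is that a valid GABA value is not expected, not that it has been shown impossible. It does not remove the point, because the conclusion is the same at both ends of the assumed ranges and the article itself names peak areas as the method.

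**The software may read a different GABA resonance.** The article does not say which one is used. With GABA assumed at 2.28 and 1.89 ppm, and neighbouring Glx and NAA signals at 2.35 and 2.01 ppm, the centres are 0.07 × 127.7 = 8.9 Hz and 0.12 × 127.7 = 15.3 Hz apart. Splittings of about 7.3 Hz spread GABA towards those neighbours, so a separation method would still have to be stated.

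**The reference may be in place.** A reader might infer that raw areas will be compared between sessions because creatine is not listed. The article does not say so. Its reference to relative concentrations is compatible with an in-spectrum reference that need not itself be an outcome. That inference is not supported.

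**The hypothesis is wider than GABA.** A reader might infer that the mechanistic hypothesis as a whole cannot be tested. The documents do not support this. The hypothesis also covers serum neurotransmitters and metabolites, the acquisition suits NAA and choline, and Glx is weakly measured rather than absent.

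**Conclusion.** The concern holds for GABA and, to a lesser degree, for Glx. On the assumed ranges, GABA contributes about 2–17% of the creatine signal it overlaps, at a separation of about 2.6 Hz, and T2 decay leaves 9–45% of signal at the stated echo time. Peak-area reading is not expected to isolate GABA anywhere in that range. For Glx, T2 loss and the small voxel make the measure weak; its phase modulation was not calculated here. All spectral constants are assumptions, since the article supplies none.

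The consequence is confined to the central-neurotransmitter part of the second hypothesis. NAA, choline, serum dopamine, norepinephrine and melatonin, the PSQI outcome and the sample size are untouched. Because MRS is secondary, this should be fixed before analysis but does not threaten the trial's main result.

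**What to change.** Do not change the sequence: the Results section reports 120 of the planned 124 participants enrolled by April 2025. Instead:

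- In Imaging Parameters, base MRS conclusions on NAA and choline, each relative to a stated in-spectrum reference such as creatine.
- Label GABA and Glx exploratory. Report them only where a prespecified separation method and fit-quality limit are met.
- Record the change, with its reason, openly and before analysis. Deleting GABA without comment this late would invite a charge of selective reporting.
- Under Hypotheses, and where the Introduction sets out the rationale, draw no conclusion about thalamic GABA as a central neurotransmitter unless such a separation is shown.

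The cost is revised wording, a stated reference in the processing of existing spectra, and a written quality rule. The downside is giving up a firm GABA/Glx result, which this sequence is not expected to supply.

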### Adverse Event Monitoring

Adverse events in this study will be closely monitored, with all details recorded in the case report forms (CRFs), to ensure that patients receive timely and appropriate management. Adverse events, including discomfort at the shallow needling site and drug-related reactions including nausea, vomiting, and dizziness, will be documented. Any serious adverse events will be promptly reported to the ethics committee to ensure participant safety.

### Statistical Analysis

In this study, data will be analyzed with SPSS (version 23.0) software. Continuous variables will be reported as means and SDs, and categorical variables will be presented as frequencies or percentages. To compare continuous variables between the 2 groups, normality and homogeneity of variance will be initially evaluated. If these assumptions are satisfied, a 2-tailed *t* test will be used. Otherwise, a nonparametric rank-sum test will be used. Categorical variables will be analyzed using the chi-square test or Fisher exact test. *P* values of .05 or less will be considered statistically significant.

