### Participants

#### Sample Size

According to the relevant literature [28], the overall efficacy rate for the control group is reported to be 79.48%, whereas the treatment group is expected to have an efficacy rate of 98%. Assuming a significance level (α) of 0.05 and a power (1-β) of 0.9, the sample size was calculated using PASS 15.0 software. A minimum of 56 participants is initially required for each group. Considering a 10% dropout rate, we plan to recruit at least 62 participants per group. Therefore, a total of 124 participants are needed for this study.

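### For continuous outcomes the protocol lets assumption checks choose between a t test and a rank-sum test and names no baseline adjustment, so the primary PSQI test is not fixed in advance and is less efficient than it could be

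*Protocol article*

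**What the plan says.** The Statistical Analysis section of the protocol article gives one rule for all continuous variables. The first step is a check: "To compare continuous variables between the 2 groups, normality and homogeneity of variance will be initially evaluated". Then: "If these assumptions are satisfied, a 2-tailed *t* test will be used". And: "Otherwise, a nonparametric rank-sum test will be used". For description, "Continuous variables will be reported as means and SDs, and categorical variables will be presented as frequencies or percentages". The section names no covariate, adjusted model, between-group estimate or confidence interval. It does not say whether post-treatment scores or changes from baseline are compared.

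PSQI is the primary outcome and falls under this rule. Under Primary Outcome Measures, "PSQI will be assessed before treatment, after treatment, and 4 weeks after treatment completion (follow-up"). The inclusion criteria require a PSQI score of 7 to 15, so a baseline value exists for everyone randomised.

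**The concern.** Two features of the rule deserve attention.

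- **No baseline adjustment is named.** Baseline PSQI is collected at no extra cost and probably predicts later PSQI. Leaving it out gives up precision. That matters here because the Discussion concedes that the planning difference may have been too optimistic and power insufficient, and because recruitment is nearly complete (120 of 124 by April 2025, per Results). A more efficient analysis is the main way left to recover power.
- **The trial data choose the test.** A t test compares means. A rank-sum test compares ranks. Under the stated rule nobody can say beforehand which of these the primary P value will refer to. If the rank-sum branch is taken, the P value does not correspond to the means and SDs that are to be reported.

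**Working it through.** **The plan's own figure.** Sample Size uses efficacy rates of 79.48% and 98%, α 0.05 and power 0.90. Two-sided, with unpooled variance:

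n = (1.960 + 1.282)² × [0.7948 × 0.2052 + 0.98 × 0.02] / (0.98 − 0.7948)² = 10.507 × 0.18269 / 0.034299 = 55.97, so 56 per group, as stated.

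This calculation does not involve PSQI scores. The document therefore gives no PSQI SD, effect size or baseline-outcome correlation, and the following are assumptions: a true difference d = 0.5 SD of the outcome, 56 evaluable per arm, and correlation ρ from 0.2 to 0.5. The entry window of 7 to 15 narrows the spread at baseline and so points to the lower part of that range.

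**Gain from adjustment.** ANCOVA multiplies the residual SD by √(1 − ρ²). The normal approximation is

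power = Φ( d√(n/2) / √(1 − ρ²) − 1.960 ), with d√(n/2) = 0.5 × √28 = 2.646.

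| ρ | √(1 − ρ²) | power | n per arm for 90% power |
|---|---|---|---|
| unadjusted | 1 | Φ(0.686) = 75% | 85 |
| 0.2 | 0.980 | Φ(0.740) = 77% | 81 |
| 0.3 | 0.954 | Φ(0.814) = 79% | 77 |
| 0.5 | 0.866 | Φ(1.095) = 86% | 64 |

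A simulation used integer PSQI scores, baseline limited to 7-15, a post-treatment SD of 3.5, and 3,000 runs per setting. ANCOVA had 76%, 78% and 86% power at ρ = 0.2, 0.3 and 0.5, against 74-75% for the t test on post-treatment scores.

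**Change scores.** Let q be the ratio of baseline SD to outcome SD. In units of the outcome variance, a change score has variance 1 + q² − 2ρq. Subtracting ANCOVA's 1 − ρ² leaves (q − ρ)², which is never negative. With equal SDs (q = 1), the same formula gives a change-score t test 55%, 61% and 75% power at ρ = 0.2, 0.3 and 0.5. With the restricted baseline of the simulation (SD 2.05, so q = 2.05/3.5 = 0.58) it reached 70%, 75% and 86%. At ρ = 0.5 that equals ANCOVA, since (0.58 − 0.5)² is close to zero. At lower ρ it falls short.

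**The preliminary checks.** They were simulated as Shapiro-Wilk in each arm plus Levene, each at 5%, in the same setting and for ρ from 0.2 to 0.7.

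- The rule moved to the rank-sum test in about 20-33% of runs, although the errors were normal before rounding.
- Power was 72-74% under the rule and 73-75% with the t test alone, a cost of about 1 point.
- The type I error under the rule was 4.5-5.5%.

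**The case against.** **The article condenses a fuller document.** An analysis plan may exist and may name covariates. That is a fair limit on any complaint of omission. It does not cover the switching rule, which the article states positively and applies to every continuous variable.

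**A reader might infer that baseline is ignored altogether.** The text does not say so. A t test on changes fits the wording, and the imaging section speaks of assessing changes in metabolites. The objection stands as far as it goes, but it does not rescue the plan, because ANCOVA is at least as efficient as a change score at every correlation.

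**A reader might blame the preliminary checks for lost power or false positives.** The simulations do not support that. Inflation of the rank-sum test with equal means was 5.2% at an SD ratio of 1.5, and 5.7% and 6.9% at ratios of 2 and 3. Nothing in the document suggests ratios that large for a score bounded at 0-21, with a narrow entry range and the same drug in both arms. If shallow needling had no effect on anyone, the two arms would share one distribution and the rank-sum test would be valid.

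**A reader might say that chance baseline imbalance biases the result.** It does not. Under randomisation the unadjusted comparison is unbiased, and its standard error already allows for chance imbalance.

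**A reader might say that the trial could end without an effect estimate.** Arm means and SDs are to be reported whichever test is used, so a crude difference can be derived. What is lacking is a named estimate with an interval that agrees with the primary P value.

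**Skewed outcomes.** For serum, sleep-recording and spectroscopy measures the document gives no distributional information, and a rank-based test may be defensible there. This stands and limits how far the fix should reach.

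**Conclusion.** The point holds as one of efficiency and prespecification, not of validity. At an assumed 0.5 SD difference and 56 per arm, baseline adjustment raises power from 75% to about 76-79% if the correlation is 0.2-0.3, and to 86% if it is 0.5. Larger gains need a higher correlation (96% at 0.7) and should not be relied on, given the restricted entry range. All of these figures rest on an effect size and correlations that the document does not supply. What does not depend on them is that ANCOVA is no less efficient than a change score, apart from a negligible loss of one degree of freedom, and that the stated rule leaves the primary test open until the data have been inspected. The change is worth making before analysis, but results under the present rule would not be invalid.

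**What to change.** By dated amendment, before outcome data are analysed:

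- For PSQI, replace the rule with one prespecified ANCOVA, or a repeated-measures model, with treatment group and continuous baseline PSQI, at a named time point.
- Report the adjusted mean difference with its 95% CI, using heteroscedasticity-robust standard errors so that no preliminary variance test is needed.
- Keep the rank-sum test as a sensitivity analysis.
- Apply the same baseline adjustment to the Hamilton Anxiety Scale and the Insomnia Severity Index. Extend it to the sleep-recording, serum and spectroscopy measures where their distributions allow, for example after transformation.

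The cost is a paragraph of analysis text and the amendment itself. No further data are needed. The amendment should carry a date and state that outcome data had not been analysed, because enrolment was almost complete by April 2025.

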**Methods:**

A single-center, prospective, assessor-blinded randomized controlled clinical trial retrospectively registered with the International Traditional Medicine Clinical Trial Registry (ITMCTR2024000409). With 2 parallel arms, the trial will be conducted at the Affiliated People’s Hospital of Fujian University of Traditional Chinese Medicine. A total of 124 participants with PI will be randomly divided into the control group and the treatment group in a ratio of 1:1 (n=62 for each group). The control group will receive 1 mg eszopiclone orally, once a day for 4 weeks. In addition to taking eszopiclone, the treatment group will receive shallow needling therapy once daily, 5 times a week, for 4 weeks. Data will be collected at 3 time slots—before treatment, after treatment, and 4 weeks after treatment—and will be analyzed using SPSS (version 23.0). The primary outcome measure is the Pittsburgh Sleep Quality Index. The secondary outcome measures include the Hamilton Anxiety Scale, Insomnia Severity Index, serum neurotransmitter detection (including dopamine, norepinephrine, and melatonin), sleep parameters, and magnetic resonance spectroscopy of the thalamus.

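### One .05 rule for 22 secondary comparisons, with hypotheses worded as proof, leaves a substantial (not likely) risk of a false objective-sleep or mechanism claim

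*Protocol article*

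**What the plan says.** The abstract names one primary outcome: "The primary outcome measure is the Pittsburgh Sleep Quality Index". Everything else is secondary.

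The Statistical Analysis section does not separate primary from secondary outcomes. For continuous variables, "If these assumptions are satisfied, a 2-tailed *t* test will be used", with a rank-sum test otherwise. It closes with a single threshold: "P* values of .05 or less will be considered statistically significant".

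The Hypotheses section turns secondary outcomes into trial hypotheses. On sleep recording: "according to the objective sleep outcome test results, the sleep treatment of the treatment group was further proved to be improved". On mechanism: "the levels of serum neurotransmitters, central neurotransmitters, and metabolites in the treatment group were significantly improved, reflecting the better regulatory effect of shallow needling".

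The outcome sections list many measures under these two statements. Polysomnography is described with "The parameters, including total sleep time, sleep latency, wake after sleep onset, sleep efficiency" and four sleep-stage percentages. For serum dopamine, norepinephrine and melatonin, "Measurements will be taken 1 day before treatment, 1 day after the completion of the treatment course, and at a 4-week follow-up". Spectroscopy is to "measure the levels of GABA, Glx, N-acetylaspartate, and choline-containing compounds in the thalamic region".

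The Discussion takes a softer line. Its opening paragraph and its paragraph on assessment methods both present the mechanism work as something to be explored.

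**The concern.** Two written statements work badly together. One threshold applies to every P value, and the hypotheses speak of proof and of significant improvement over sets of eight (sleep recording) and ten (serum and spectroscopy) comparisons. Under the written threshold, a nominally significant result on one of them could be presented as support for the corresponding hypothesis.

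This matters more than usual here. The primary outcome is a self-reported questionnaire, participants are not blinded, and there is no sham. The limitations paragraph of the Discussion cites objective outcome measures as one of its safeguards, next to blinded assessors and statisticians and a follow-up period. If a chance finding among those objective measures were read as confirmation, the safeguard would lend false weight to a primary result that is itself open to expectation effects.

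For several serum and spectroscopy analytes the article also does not say which direction counts as improvement. The Introduction does so in part: it links low GABA to hyperarousal.

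**Working it through.** **Figure in the plan.** The article states no family-wise error rate, so there is none to reproduce. Its only relevant figure is the threshold of .05, two-sided. For one test with no true effect, that means 5% in either direction and 2.5% in favour of treatment.

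**Step 1: count the comparisons** (measures × post-baseline times, from the outcome sections).

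| Domain | Measures | Post-baseline times | Comparisons |
|---|---|---|---|
| Hamilton Anxiety Scale | 1 | 2 | 2 |
| Insomnia Severity Index | 1 | 2 | 2 |
| Polysomnography (total sleep time, latency, wake after sleep onset, efficiency, REM%, N1%, N2%, N3%) | 8 | 1 | 8 |
| Serum (dopamine, norepinephrine, melatonin) | 3 | 2 | 6 |
| Thalamic spectroscopy (GABA, Glx, N-acetylaspartate, choline compounds) | 4 | 1 | 4 |
| **Total** | | | **22** |

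The objective-sleep and mechanism comparisons number 8 + 6 + 4 = 18. PSQI is primary and is not counted.

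**Step 2: independent tests, no true effect.** The chance of at least one P ≤ .05 among k tests is 1 − 0.95^k. Counting only results that favour treatment, it is 1 − 0.975^k.

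- k = 22: 1 − 0.95^22 = 0.676; expected false positives 22 × .05 = 1.1
- k = 18: 1 − 0.95^18 = 0.603; favouring treatment, 1 − 0.975^18 = 0.366
- k = 8: 1 − 0.95^8 = 0.337; favouring treatment, 1 − 0.975^8 = 0.183

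**Step 3: correlated tests.** The outcomes are related (stage percentages sum to 100, and serum and the scales are measured repeatedly), so independence is the upper end. With a common correlation ρ, write each statistic as Z = √ρ·U + √(1−ρ)·E, with U shared and E separate. The chance of at least one rejection is 1 minus the average over U of p(U)^k, where p(U) is the chance that one test does not reject, given U. The correlations are assumptions.

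| Set | Event | ρ = 0 | ρ = 0.5 | ρ = 0.9 |
|---|---|---|---|---|
| All 22 | either direction | 68% | 44% | 16% |
| 18 objective-sleep and mechanism | either direction | 60% | 40% | 15% |
| 18 objective-sleep and mechanism | favouring treatment | 37% | 20% | 7.5% |
| 8 polysomnography | favouring treatment | 18% | 13% | 6% |
| One test | favouring treatment | 2.5% | 2.5% | 2.5% |

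**Step 4: sensitivity.** A more structured assumption uses correlation 0.3 to 0.6 within a domain, 0.6 to 0.8 for the same measure over time, and 0 to 0.3 between domains. It gives 48% to 62% for the 22 and 42% to 55% for the 18 in either direction, and 21% to 31% for the 18 favouring treatment.

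The count could also be higher. Left and right thalamus analysed separately gives 22 + 4 = 26 (74% if independent). If the Follow-Up section is read literally as repeating every measure, polysomnography and spectroscopy add 8 + 4, giving 34 (83% if independent).

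**The case against.** **The outcomes are labelled secondary, and detail may sit elsewhere.** An ordered list, an alpha split or a rule on how many tests must succeed is commonly left to a full protocol or analysis plan, and neither is shown. This stands: the absence of a multiplicity procedure is not the point. What remains is the conflict between statements that the article does make. An analysis plan that called these outcomes exploratory would itself conflict with the Hypotheses section.

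**The hypotheses are expectations, not decision rules.** The second one joins serum, central neurotransmitters and metabolites, so read strictly one stray P value would not satisfy it. This has some force: the chance of at least one significant result is an indicator of risk, not the exact error rate of a defined test. The wording is still confirmatory, and nothing in it prevents one result being cited in support.

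**Stronger readings.** A reader might infer that a false confirmation is likely. The figures do not support that. For the 18 comparisons concerned, at a correlation of 0.5, the chance is 40% in either direction and 20% in favour of treatment. A reader might also apply the either-direction rate to objective sleep, which for the eight parameters is 25% at a correlation of 0.5. The hypothesis there is improvement, so only results favouring treatment count, and the rate is about 13%. The either-direction figure is arguable only for serum and spectroscopy analytes with no stated direction. Finally, it would be wrong to say that the article never treats the mechanism work as exploratory, because the Discussion does. That shows the inconsistency, and it also points to the remedy.

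**Conclusion.** The point holds as a conflict within the article. A single .05 rule, set beside hypotheses that speak of proof and significant improvement, would license secondary claims with error well above the single-test rate, while the Discussion calls the mechanism part exploration.

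For results that favour treatment, the risk across the 18 objective-sleep and mechanism comparisons is 3 to about 15 times the 2.5% of one test (7.5/2.5 = 3; 37/2.5 = 14.8). For polysomnography alone it is about 2.4 to 7 times (6/2.5 = 2.4; 18/2.5 = 7.2). That is a substantial risk of a false objective or mechanistic confirmation of an unblinded, self-reported primary outcome; it is not the expected result.

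The size rests on no true effect in any of these outcomes, on the count of 22 (18 in the narrower set), and on assumed correlations from 0 to 0.9. The direction of the conclusion does not depend on the correlation chosen; the size does.

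**What to change.** - **Statistical Analysis:** replace the blanket sentence with a statement that the two-sided .05 level supports a claim only for the primary PSQI comparison. State that the secondary scale, polysomnography, serum and spectroscopy comparisons are exploratory, reported as between-group differences with 95% confidence intervals and nominal P values. PSQI has two post-baseline assessments, so the sentence should say which comparison is meant.
- **Hypotheses:** replace the language of proof and significant improvement for objective sleep, neurotransmitters and metabolites with exploratory wording consistent with the Discussion.
- **Optional:** if the sponsor wants a confirmatory secondary claim, it should name its own short ordered list before analysis. The documents give no basis for prescribing a particular order.

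The cost is wording only: no new participants, visits or measurements. The downside is that polysomnography, serum and spectroscopy results can no longer be claimed as confirmed effects. The change should be dated and made before the data are analysed. The Results section reports 120 of the planned 124 participants enrolled by April 2025, so time is short.
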